## Abstract

**Background:**

Childhood obesity is not only associated with adult obesity but also with increased risk of adult onset of type 2 diabetes and subsequent coronary heart disease. The potential effects of school-based health intervention programmes on cardiovascular risk and surrogate markers are unclear, as only few studies have attempted to investigate a complete risk profile including a detailed laboratory analysis or micro- and macrovascular function. In this study a comprehensive school-based randomized intervention programme will be investigated in 10-14-year old children addressing the influence of lifestyle intervention on inactivity, cardiometabolic risk factors and early signs of vascular disease.

**Methods/Design:**

15 secondary schools in Southern Germany are randomly assigned to intervention or control schools. Children in the fifth grade (10-11 years) will be observed over four years. The study combines a school-based with a home-based approach, aiming at children, teachers and parents. The main components are weekly lifestyle-lessons for children, taught by regular classroom teachers to increase physical activity in- and outside of school, to improve eating patterns at school and at home, to reduce media consumption and to amplify well-being. In 4-6 annual meetings, teachers receive information about health-related topics with worksheets for children and supporting equipment, accounting for school-specific needs and strategies. Parents' trainings are provided on a regular basis.

All examinations are performed at the beginning and at the end of every school year. Anthropometry includes measurements of BMI, waist and upper arm circumferences, skinfold thickness as well as peripheral blood pressure. Blood sampling includes lipid parameters, insulin, glucose, hsCRP, adiponectin, and IL-6 as well as testosteron and estrogen to determine maturation status. Vascular function is non-invasively assessed by measuring arterial stiffness in large arteries using a sphygmograph and by analysing arteriolar and venular diameters in the retinal microcirculation using a non-mydriatric vessel analyser. A questionnaire is filled out to determine daily physical activity, motivational factors, dietary habits, quality of life (KINDL-R) and socio-economic data. Physical fitness is assessed by a six-item test battery.

**Discussion:**

Our study aims to provide a feasible long-term intervention strategy to re-establish childhood health and to prevent obesity-related cardiovascular dysfunction in children.

**Trial Registration:**

NCT00988754

## Background

### Cardiovascular Disease Epidemiology

According to the World Health Organisation, cardiovascular disease (CVD) is the leading cause of mortality worldwide and is responsible for 30% of all global deaths [1]. In adults, a high body mass index is the main reason for increased mortality [2]. Adult and childhood overweight and obesity are often related to manifestation of metabolic diseases such as type 2 diabetes, hypertension and hyperlipidemia [3-6]. Overweight and obesity can often be tracked from childhood to adulthood [7,8] and childhood obesity has been associated with premature death [9,10] and adult coronary heart disease [11,12].

### Eating Pattern, Physical Activity and Mortality

The worldwide increase in obesity is related to changes in eating patterns and reduced physical activity. Caloric-dense foods with high satured fat and refined carbohydrates have replaced traditional diets with vegetables, fruits and whole grain products. The increase in fast-food restaurants [13] and "eating out" is associated with a higher risk to become overweight [14]. Sugar-sweetened beverages induce weight gain and increase the incidence of type 2 diabetes [15]. Unhealthy eating patterns are often combined with less physical activity.

It is estimated that 60% of the population all over the world is inactive. Physical inactivity is estimated to be the main cause for approximately 21-25% of breast and colon cancers, 27% of diabetes and approximately 30% of the ischaemic heart disease burden [16]. Physical inactivity and low physical fitness is associated with a higher risk for hypertension and stroke [17] and type 2 diabetes [18], independent of overweight and obesity.

Results of the German Health Interview and Examination Survey for Children and Adolescents (KiGGS) have shown that only 28% of boys and 17% of girls reach the current recommendation of 60 minutes or more of physical activity each day (CDC 2010, WHO 2010). Low activity is particularly prevalent in girls, as well as in children with low socio-economic status or ethnic background [19]. In the United States only 15% of the children go or bike to school (CDC 2010). In UK, the average annual walking distances has declined by 24% and the annual distance cycled by 31% from 1985 to 1995 in adolescents aged 15-19 years [20].

These lifestyle changes lead to obesity, chronic diseases and premature mortality [21].

### Childhood Obesity, Physical Activity and Inflammation

The association between c-reactive protein (CRP) and future coronary events has been demonstrated for adults [22]. CRP is a sensitive marker of inflammation and it plays a causal role in the process of inflammation [23]. In healthy prepubertal children an association between CRP, fasting insulin, dyslipidemia, blood pressure and adiposity has been found [24]. In the Cardiovascular Risk in Young Finns Study, high CRP levels were one of the determinants in youth for the incidence of adult metabolic syndrome [25]. In obese and normal weight adolescents, regular aerobic exercise has been shown to reduce CRP concentrations [26,27].

Also interleukin-6 (IL-6) plays a key role in the pathogenesis of CVD [28]. It affects platelet reactivity as well as endothelial function [29]. IL-6 is secreted to a large extend in adipocytes of visceral fat and is therefore elevated in obese individuals [30,31]. In addition, IL-6 seems to be negatively associated with physical activity [32] and regular exercise has the potential to decrease IL-6 serum levels [27].

The adiponectin, an adipokine, is reduced in obesity and type 2 diabetes. Low plasma adiponectin levels are a sign of decreased insulin sensitivity, adipocyte dysfunction and an important link to the development of vascular disease [33-35]. In children, adiponectin is also inversely correlated with BMI, fat mass and fasting insulin [31]. The effects of physical activity on adiponectin levels in children, however, are still unclear.

In summary, physical activity and physical fitness seem to be protective against low grade inflammation, but more longitudinal research is needed to clarify the association between physical activity, physical fitness, obesity and low grade inflammation in children [36].

### Childhood Obesity, Physical Activity and Atherosclerosis

Physical inactivity has been shown to play a key role in the development of obesity-related atherosclerotic cardiovascular disease and may represent an important link between obesity, inflammation, insulin resistance and early atherosclerosis in adults [37]. However, the association among children is less clear and has only been examined by a handful of studies [38]. Increased carotid intima-media thickness (IMT) and impaired flow-mediated vasodilation (FMD) have previously been documented in young obese subjects which can be restored after a six-months exercise programme [26]. Furthermore, in obese children, a higher arterial wall stiffness has previously been described [39]. Pulse wave velocity (PWV) is a validated index of arterial stiffness which can easily be examined by non-invasive applanation tonometry. In healthy prepubescent children, increased PWV is associated with obesity and decreased cardiorespiratory fitness [40].

The retinal microcirculation can be analysed non-invasively, which offers a unique opportunity to examine the effects of obesity on small brain vessels. In adults, obesity has been associated with a wider retinal venular diameter and a lower arterio-venous ratio (AVR). In several large adult cohort studies, AVR has been shown to be a valid index for an increased risk of hypertension, stroke and higher cardiovascular mortality [41,42]. Similar to findings in adults, childhood obesity is associated with retinal venular dilatation and lower AVR [43], and higher childhood blood pressure has been linked to retinal arteriolar narrowing [44]. The investigation of early macro- and microvascular impairments in childhood obesity are important measures to define obesity-related early signs of vascular disease. No study to date has examined the effects of a lifestyle intervention on the retinal microcirculation in children. Therefore, it is of great importance to elucidate whether early vascular alterations in children can be restored by a school-based intervention programme.

### Media Use, Physical Activity and Health

Over the last twenty years, the amount of time children spend in front of television, computer and video games has increased and serious negative health effects such as violent behaviour, substance abuse (alcohol, smoking), decreased school performance, poor body image and obesity become more apparent [45]. Television affects food consumption of children [46] and displaces physical activity [47]. Reducing media use has been shown to be an effective measure in preventing obesity [48,49] and improving educational achievements [50]. Moreover, increased physical activity has been demonstrated to combine health benefits with reduced substance abuse [51].

### Effects of School-based Physical Activity Interventions

The school environment has great potentials to introduce and encourage a healthy lifestyle in children across all socio-economic and ethnic borders. However, it becomes more and more evident that the school-intervention approach needs to be combined with a family-based health education [52]. Several lifestyle intervention programmes have been conducted in school settings, but the results have been inconsistent and have primarily focused on basic measures of obesity such as BMI or skinfold thickness [53-55]. Although anthropometric end points are fundamental, more attention needs to be drawn to obesity-related cardiovascular risk factors such as lipid profiles, adipocytokines, inflammation and insulin metabolism. Some more recent studies have demonstrated the beneficial effects of a school-based intervention on serum lipids and inflammatory markers in obese children [56]. As childhood obesity is associated with signs of early atherosclerosis, school-based interventions should be validated with a long follow-up regarding improvement of behaviour (diet, exercise), body composition, fitness, and early cardiovascular risk profile.

## Methods/Design

### Objectives

The study aims to implement a comprehensive randomized controlled school- and family-based lifestyle-intervention trial (RCT) in secondary schools to analyse and improve cardiometabolic risk factors and vascular function in large and small vessels of children aged 10 to 11 years over a period of four years by increasing physical activity and physical fitness, psychological well-being, and the motivation to exercise.

### Primary Objectives

1. Primary outcomes of the intervention were defined as an increase in number of days with physical activity >60 min/day (in- and outside of school).

### Further Objectives are

2. Prevention of early macro- and microvascular impairments (arterial stiffness and retinal vessel diameter).

3. Reduction of cardiometabolic risk factors (Triglycerides, LDL-cholesterol, HDL-cholesterol, glucose, hsCRP, IL-6, adiponectin).

4. Reduction of the prevalence of obesity (BMI, waist circumferences, total skinfold thickness).

5. Improvement in motor abilities and physical fitness (six-item test battery).

6. Normalisation in systolic and diastolic blood pressure.

7. Increase in health-related quality of life (HRQoL) measured by a child questionnaire (KINDL-R).

### Secondary Objectives

To analyse the correlation between arterial stiffness and retinal vessel diameter with childhood obesity and interventional improvements of cardiovascular risk factors. In addition, the association between arteriel stiffness, retinal vessel diameter and lifestyle factors (physical activity, eating patterns, smoking are elucidated.

### Study Groups/Recruitment

Figure 1 shows the flow diagram of the recruitment process. All secondary schools in the greater district of a city in Southern Germany were asked to take part by written invitations (65 schools), an advertisement in a local newspaper and via local radio announcements. Recruitment of participating schools was based on the willingness to take part over four years and to be randomized either to an intervention school with a lifestyle intervention programme or a control school. 12 urban schools agreed to take part in response to the individual invitations and interviews, 6 schools answered the advertisement in the newspaper. From these, 3 schools were excluded because they were located outside of the study area (distance >30 km). In all, 15 schools with 32 classes agreed to take part and were randomized. The children of 7 secondary general schools and 8 intermediate schools gave written consent from their parents. 12 schools are located in the city area and three schools are located in communities outside the greater city area. The study protocol was approved by the ethics board of the faculty of medicine of the Technische Universitaet Muenchen. The study takes into account the principles set out in the Helsinki declaration (Seoul, 2008) (2119/08).

**Figure 1 F1:**
[figure not shown]
**Flow of School Classes**.

### Statistical Analysis

Fifteen schools with about 700 pupils attending fifth grade agreed to participate in the study and were randomly assigned to either intervention (n = 8 schools) or control group (n = 7 schools). Aim of the study is to increase the number of days per week a child is active, defined as days with physical activity of more than 60 minutes. This outcome is assessed in a standardized questionnaire at the beginning and at the end of the study. The primary analysis will be a comparison of the proportion of children with an increase in the number of active days per week between both study groups considering the effect of clustering.

Due to the small number of cluster (n = 15) methods analysing the data on the individual level and accounting for the intracluster correlation (as e.g. GEE [57,58]) or adjusted chi-square test [57] are not applicable [59]. Therefore the primary endpoint will be analysed on the cluster level. Mean proportions of children with increased activity assessed at school level will be compared between control and intervention schools as proposed by Donner and Klar [57] for the analysis of binary data in cluster randomized trials with a small number of clusters. A two-sample t-test will be performed to compare both groups. The t-test was shown to give valid results in such settings, even when assumptions (normality, equality of variances) are moderately violated [60]. Since drop-outs of children will be mainly caused by school changes and therefore are assumed to be independent of the outcome, a complete case analysis will be performed to investigate the primary endpoint. Yearly examinations will be considered to investigate the pattern of missing values. If the assumption of random drop-outs does not hold, adequate imputation methods will be used. The primary analysis will be performed on a two-sided level of significance of α = 0.05.

All secondary endpoints will be analysed on the cluster level. 95% confidence intervals will be presented for relevant measures. For binary data, means of school level proportions, for quantitative data means of school level means will be compared using two-sample t-tests. All secondary endpoints will be analysed in an explorative manner on a two-sided level of significance of α = 0.05, so no adjustment for multiple comparisons will be conducted.

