Numerous investigations have demonstrated a decrease in physical activity and physical fitness in children. The school environment can play an important role in increasing the physical activity of children. The way to school is an important part of daily activity and facilitates children to reach the current recommendations [73]. Therefore, active commuting should be supported by schools and parents. An increasing number of children in Germany spend the whole day at school. Schools should therefore aim to offer physical activity practice in regular lessons, to carry out sufficient physical exercise lessons with qualified teachers, as well as to provide sufficient physical activity proposals during breaks and in the afternoon. Beyond these school-based efforts, the prevention programme will encourage family-based physical activities and reinforce the cooperation between schools and sports clubs. In addition, the programme educates children and parents on healthy food and eating patterns in order to improve their skills to achieve a healthy lifestyle. Advice is given to the schools' administrations to implement healthy food in school vending machines and school meals.

Over the last decade, the growing influence of internet and social networks as well as the increase of media use has augmented enormously, especially in children. School-based prevention programmes therefore need to include media-competence-training to prevent a further decline in physical activity, negative effects on school performance or well-being.

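### The primary analysis scores active days only as increased or not and ignores the collected baseline count. It is valid and powered as stated, but less sensitive than a baseline-adjusted analysis of the same data.

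*Protocol article*

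**What the plan says.** The Primary Objectives section defines the outcome as "an increase in number of days with physical activity >60 min/day (in- and outside of school"). The Statistical Analysis section repeats that the aim is to "increase the number of days per week a child is active, defined as days with physical activity of more than 60 minutes". Both describe a count, which can run only from 0 to 7 days per week.

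The Statistical Analysis section then fixes the primary analysis as a "comparison of the proportion of children with an increase in the number of active days per week between both study groups". On timing it says: "This outcome is assessed in a standardized questionnaire at the beginning and at the end of the study". Schools are "randomly assigned to either intervention (n = 8 schools) or control group (n = 7 schools"), and their proportions are compared by a two-sample t-test at two-sided 0.05. No baseline adjustment is described, and no reason is given for reducing the count to yes or no. Quantitative secondary endpoints are to be compared as means of school means with the same test, and all secondary endpoints are exploratory.

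Power Considerations takes a standard deviation of 9 percentage points (pp) for the school-level proportion, observed in a similar trial in younger children. It claims over 80% power for a difference of 15 pp.

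**The concern.** The scoring discards information in three ways, and the analysis ignores a strong predictor.

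- **Ceiling.** A child active on all 7 days at baseline cannot increase and is a non-success in either arm.
- **Stability equals decline.** A child who stays at 5 days scores the same as one who falls from 5 to 3. Follow-up covers four years from age 10–11, and the Discussion names puberty as a time when inactivity often begins, so declines are plausible.
- **Size of gain is lost.** One extra day counts as much as five.
- **Baseline dependence.** A child who starts low has more room to rise and regresses upward; a child who starts high does the opposite. With 15 schools, some chance imbalance in baseline days is to be expected, and the stated comparison does not remove it.

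At stake is the sensitivity and precision of the one confirmatory test. The baseline count is already collected, so the loss can be avoided.

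**Working it through.** **1. The plan's own power figure.** Inputs from Statistical Analysis and Power Considerations: 8 and 7 schools, difference 15 pp, SD 9 pp, two-sided 0.05.

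- Effect size d = 15/9 = 1.67.
- Noncentrality = d × √(8×7/15) = 1.667 × 1.932 = 3.22, with 13 degrees of freedom and critical t = 2.16.
- Power = 84.5%. The stated figure of over 80% reproduces.
- The SD was observed on this same yes/no endpoint, so this power already contains any loss from dichotomising.

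**2. Size of the ceiling.** The Background cites a national survey in which "only 28% of boys and 17% of girls reach the current recommendation of 60 minutes or more of physical activity each day". If those rates applied to this sample with equal numbers of boys and girls, 0.5 × 28% + 0.5 × 17% = 22.5% would be at 7 days. At most about 77.5% of children could then count as successes. The protocol gives no such figure for its own pupils.

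**3. Sensitivity of three analyses of the same data.** The protocol does not give the distribution of days, the baseline–follow-up correlation, the ICC or the control drift, so these are assumed:

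- 8 v 7 schools with 47 children each (about 700/15);
- days from 0 to 7 derived from a latent normal variable;
- 10–22% at 7 days at baseline, correlation 0.3–0.5, ICC 0.01–0.03, and control drift of 0 or −0.7 day;
- a latent shift of 0.7 day in the intervention arm.

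The simulated school SD of the proportion was 7–9 pp, close to the plan's 9 pp. Each analysis ends in a t-test on 15 school values.

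| Analysis | Power |
|---|---|
| Proportion increased, unadjusted (as planned) | 40–74% |
| Proportion increased, adjusted for baseline days | 60–83% |
| Mean days, adjusted for baseline days | 76–96% |

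Unconditional type I error was about 5% for all three. A separate run under the same assumptions gave 38–75%, 58–83% and 73–95%, so the limits are good to about 3 points. In a check run, the 0.7-day shift moved the proportion by about 9–12 pp. That is less than the 15 pp of the power statement, so 40–74% does not contradict 84.5%.

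**4. The same comparison at about the planned effect.** With the shift set so that the planned test has about 81–89% power (ICC extended to 0.05), mean change in days has about 90–98% and baseline-adjusted mean days about 97–99.9%. The ratio of squared standardised effects is 0.58–0.84 against mean change (16–42% of information lost). Against baseline-adjusted days it is 0.35–0.62 (38–65% lost).

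**5. Chance baseline imbalance.** Assume a child SD of 1.9–2.2 days, ICC 0.025 and 47 children per school.

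- Variance of a school mean = SD² × (0.025 + 0.975/47) = 0.0457 × SD².
- SE of the difference between arms = SD × √(0.0457 × (1/8 + 1/7)) = 0.111 × SD = 0.21–0.24 day.
- A difference of 0.4 day or more in either direction therefore occurs in about 6–10% of randomisations.

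With no true effect, when one arm starts about 0.3–0.4 day lower by chance, the unadjusted difference in proportions is shifted by about 3–5 pp in that arm's favour. Adjustment removes nearly all of this.

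**The case against.** The strongest defence is that the proportion of children who increase is a legitimate prespecified endpoint. It matches an aim worded as an increase, is analysed by a recognised method for few clusters, and is powered on an SD observed on the same variable. All of that stands. Ceiling children fail in both arms, so they cause no bias. Randomisation keeps the type I error at 5%, so the imbalance in step 5 is a conditional problem in a minority of draws, shared by any unadjusted analysis. Replacing the endpoint would also give up the only planning SD in the document.

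Three stronger readings are tempting and not supported:

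- **That about half the power is lost.** At about the planned effect the gap is roughly 5–19 percentage points. Something near half is defensible only as lost information against baseline-adjusted days, and only under assumed inputs. Part of the gain in step 3 comes from the covariate alone, not from undoing the dichotomy.
- **That preventing decline is a trial aim the endpoint misses.** The words "to prevent a further decline in physical activity" in the Discussion belong to a general remark on media training in school programmes. The stated activity objective is to increase it.
- **That 17–28% of these pupils are at the ceiling.** Those are national survey rates, not trial data.

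It can also be said that covariate adjustment is often left to an analysis plan that is not shown. Here, however, the article itself states the primary comparison and its test in full, as unadjusted school proportions.

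**Conclusion.** The point holds as a matter of efficiency and interpretation. The planned test is valid and its power statement is right for 15 pp with an SD of 9 pp. It nevertheless reduces a count to yes or no and ignores a baseline value that predicts the outcome. Under the assumed inputs, baseline adjustment alone raises power from about 40–74% to 60–83%, and adjusted mean days raise it to 76–96%. These figures depend on an assumed 0.7-day shift and on a distribution, correlation and ICC that the protocol does not give. The direction was the same in every scenario run; the size is uncertain. Adjusting for baseline is the well-supported part. Changing the primary variable is more debatable. This is a recommended improvement, not an error that must be corrected.

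**What to change.** Amend the primary analysis before any end-of-study data are seen. Keep the school as the unit and keep the two-sample t-test.

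- **Minimum.** For each child, take as expected value the proportion increasing among all children with the same baseline days, ignoring arm. Average observed minus expected within each school and compare the 15 school values. The endpoint stays, and the existing power calculation stays and becomes conservative.
- **Preferred.** Make the primary variable the number of active days at the end of the study. Regress it on baseline days within school, ignoring arm, average the residuals (calculated without removing school means) per school, and compare the 15 averages. Report the proportion increasing as supportive.

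The cost is amendment wording and no new data. The preferred version has one real downside: the 9 pp SD does not carry over to mean days, so a planning SD must be re-derived from the earlier trial's data and the power restated.

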### Power Considerations

In a similar trial in younger children (JUVENTUM I, currently under review) a standard deviation for the school level proportion of children increasing their activity of 9 percentage points was observed in both groups. Assuming this standard deviation, the study is sufficiently powered (over 80%) to detect a difference between control and intervention group of 15 percentage points, translating to an effect size of 1.67, on a two-sided level of significance of α = 0.05.

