### Anthropometrics

All clinical examinations are conducted by trained medical staff according to standardized procedures. Height and weight are measured at the beginning of the programme and annually at the end of a school year with minimal clothing without shoes. Weight is measured to the nearest 0.1 kg by using a calibrated balance scale. Height is measured to the nearest 0.1 cm by a rigid stadiometer. Body mass index (BMI) may then be calculated as weight in kilogramms divided by the square of height in meters. The BMI-SDS (BMI-standard deviation score) is determined using the LMS-method [62]. Reference data from German children are used [63]. Children with a BMI lower than the 10^th ^percentile are classified as underweight, between the 10^th ^to 90^th ^percentile as normal, between the 90^th ^and 97^th ^percentile as overweight, and above the 97^th ^percentile as obese. The pubertal development stage is being determined by estrogen and testosteron levels. Waist circumference is measured on bare skin in a standing relaxed position in a horizontal line just above the navel, the upper arm circumference is examined half way between the olecranon process of the ulna and the acromion process of the scapula with a non-stretchable tape measure. Skinfold thickness as a surrogate of subcutaneous fat is measured at four sites (m. bizeps, m. triceps, subscapular and supra-iliacal) according to the guidelines of the manufacturer. Blood pressure is measured by using a validated protocol [64] at the right brachial artery in the fossa cubitalis after the subjects rest for 5 min in a supine position. Measures of systolic and diastolic blood pressures and the cuff sizes are to be recorded.

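### Quantitative secondary endpoints are compared by t-tests of school means with no baseline adjustment, which leaves the 8 v 7 school comparison imprecise and open to chance baseline imbalance

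*Protocol article*

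**What the plan says.** The Statistical Analysis section of the protocol article sets one rule for everything beyond the primary endpoint: "All secondary endpoints will be analysed on the cluster level". For continuous measures it adds that "for quantitative data means of school level means will be compared using two-sample t-tests"; binary measures are handled in the same way with school proportions. These endpoints are to be "analysed in an explorative manner on a two-sided level of significance of α = 0.05", with 95% confidence intervals for relevant measures. The section does not list them. I take them to be the items under Further Objectives: vascular measures, cardiometabolic markers, adiposity, fitness, blood pressure and quality of life.

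Baseline values are collected. The Abstract places all examinations at the start and the end of each school year. Course of Measurements has them repeated yearly for four years. The Anthropometrics section states that "Height and weight are measured at the beginning of the programme and annually at the end of a school year".

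Only the primary endpoint is expressly tied to baseline, because it counts children whose number of active days has risen.

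**The concern.** Fifteen schools are few. They include 7 secondary general and 8 intermediate schools, and 12 lie in the city area and 3 outside it (Study Groups/Recruitment). Randomisation balances such a set only on average, so in any one allocation the arms may start apart on a given measure. If follow-up means are compared without regard to baseline, part of that starting difference appears in the estimate, where it can look like an effect or hide one. Variation between schools that baseline could have explained also stays in the error term and widens the intervals.

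At stake are the precision and readability of the planned secondary comparisons, including the vascular measures. The validity of the tests and the primary analysis are not affected.

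**Working it through.** **The plan's own figure.** Under Power Considerations, "a standard deviation for the school level proportion of children increasing their activity of 9 percentage points was observed in both groups", and the target is "to detect a difference between control and intervention group of 15 percentage points". The effect size is 15/9 = 1.67. With 8 v 7 schools there are 8 + 7 − 2 = 13 df, and the noncentral t distribution gives 84.5% power at two-sided α = 0.05. The stated power of over 80% is reproduced. It concerns the primary endpoint only and is not altered by what follows.

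**Unadjusted secondary comparison, in school-level SDs.**
- Standard error of the arm difference: √(1/8 + 1/7) = 0.5175.
- 95% half-width: 2.160 × 0.5175 = 1.12.
- Difference detectable with 80% power: 1.57.

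**Chance imbalance at baseline.** The arm difference in baseline school means has the same SD, 0.52. Under normality, it exceeds 0.5 SD with probability 2 × [1 − Φ(0.5/0.5175)] = 33%, and 1 SD with probability 5%. With equal SDs at both times, about r times the imbalance passes into an unadjusted comparison of follow-up values. For example, at r = 0.7 an imbalance of 0.5 SD shifts the estimate by 0.7 × 0.5 = 0.35 SD.

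**Adjustment at school level.** Regress the school follow-up mean on group and school baseline mean (12 df, critical t 2.179). The variance factor is (1 − r²) × 12/11, where 12/11 allows for chance imbalance in the covariate with 15 schools. The half-width is 2.179 × 0.5175 × √[(1 − r²) × 12/11]; at r = 0.7 that is 2.179 × 0.5175 × √0.556 = 0.84.

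**Change scores.** The variance factor is 2(1 − r) on 13 df, assuming equal SDs at both times.

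The article gives no school-level r, so a range is shown:

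| r (assumed) | Half-width, unadjusted follow-up | Half-width, change | Half-width, baseline-adjusted | Detectable difference, adjusted |
|---|---|---|---|---|
| 0 | 1.12 | 1.58 | 1.18 | 1.65 |
| 0.3 | 1.12 | 1.32 | 1.12 | 1.57 |
| 0.5 | 1.12 | 1.12 | 1.02 | 1.43 |
| 0.7 | 1.12 | 0.87 | 0.84 | 1.18 |
| 0.8 | 1.12 | 0.71 | 0.71 | 0.99 |
| 0.9 | 1.12 | 0.50 | 0.51 | 0.72 |

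The standard error is multiplied by √0.818 = 0.90, √0.556 = 0.75 and √0.393 = 0.63 at r = 0.5, 0.7 and 0.8. Adjustment breaks even with the unadjusted test at r of about 0.31.

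**Simulation** (10,000 runs per r, true difference 1 school-level SD). Power is about 43% unadjusted. Adjusted, it is 40%, 44%, 51%, 66%, 81% and 97% at r = 0, 0.3, 0.5, 0.7, 0.8 and 0.9. Mean estimates are about 1.00 for every method, so none is biased.

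**The case against.** The strongest reply is that the text fixes the unit and the test but not the quantity averaged. Most of the further objectives are worded as change, and the primary endpoint is itself a within-child change, so the school means could be means of change, which use baseline. This stands: a reader might infer that unadjusted follow-up values are meant and that baseline plays no part, but the article does not say so. It does not dispose of the point. Change scores are less precise than follow-up values below r = 0.5 and match baseline adjustment only from about r = 0.8.

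A second reply is that the endpoints are exploratory, that a simple analysis suits 15 clusters, and that detail may sit in an analysis plan that is not shown. The exploratory label does limit the weight. But the article names the test, and that test has no place for a covariate, so this is a stated choice and not merely an omitted detail. Baseline adjustment can also be done within the cluster-level approach that the article prefers.

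A third reply is that the gain is uncertain. That also stands. Strong tracking within children and differences between schools at entry are plausible, but the article gives no data on either for these endpoints. Its Background mentions tracking only for overweight and obesity into adulthood, which is not a school-level correlation over four years.

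**Conclusion.** The point holds with moderate weight. As written, the quantitative secondary analyses have no baseline covariate. With 8 v 7 schools they carry a half-width of 1.12 school-level SDs on follow-up values, and a chance baseline difference with an SD of 0.52. School-level adjustment would narrow the interval by about 9%, 25% and 37% at r = 0.5, 0.7 and 0.8 (1.02, 0.84 and 0.71 against 1.12), and widen it by about 5% at r = 0 (1.18 against 1.12). These figures assume normal school means and equal SDs at both times, and r itself is an assumption.

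Four stronger readings are not supported:
- That the planned test is biased or has the wrong type I error. Under randomisation it is valid.
- That precision is lost for every endpoint. Below r of about 0.31 school-level adjustment does slightly worse.
- That the gain is the full √(1 − r²), or 0.87, 0.71 and 0.60 at those three correlations. This leaves out the 12/11 factor.
- That all these endpoints are what the Discussion calls the study's main strength. That remark covers only the macro- and microvascular measures.

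**What to change.** State, for each quantitative secondary endpoint, whether the follow-up value or the change is analysed, and adjust for baseline while keeping the school as the unit. Fix one of two routes in advance:

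1. Regress the school follow-up mean on group and school baseline mean (12 df), and report the adjusted difference with its 95% confidence interval.
2. Regress each child's follow-up value on his or her own baseline value, leaving group out of the model. Average the residuals by school, and compare the 15 school means by two-sample t-test with a 95% confidence interval.

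For binary secondary endpoints, use the analogous observed minus expected school proportions from a baseline-adjusted logistic model without group.

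The tabulated gains belong to route 1. The gain from route 2 depends on how closely the child-level slope matches the school-level one, and the article gives no data from which to compute it.

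The cost is a change of wording and slightly more analysis work, with no new data. Route 1 also costs 1 df and a small loss of precision for endpoints with r below about 0.31.
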